## Abstract

Autistic spectrum disorder (ASD) is a common developmental disorder in children. The latest non-intrusive brain stimulation (NIBS) technology—transcranial pulse stimulation (TPS)—has been proven effective in older adults with mild neurocognitive disorders and adults with major depressive disorder. Nonetheless, there is so far no robust randomized controlled trial (RCT) conducted on adolescents with ASD nationwide. This study proposes a two-armed (verum TPS group vs. sham TPS group), double-blinded, randomized, sham-controlled trial. Both groups will be measured at four timepoints, namely, baseline (T1), 2 weeks immediately after post-TPS intervention (T2), and at the 1-month (T3) and 3-month (T4) follow-ups. Thirty-four subjects, aged between 12 and 17, diagnosed with ASD will be recruited in this study. All subjects will be computerized randomised into the verum TPS group or the sham TPS group on a 1:1 ratio. All subjects will undertake functional MRI (fMRI) before and after the 2-weeks TPS interventions, which will be completed in 2 weeks’ time. This will be the first RCT evaluating the efficacy of TPS adolescents with ASD in Hong Kong. Clinical Trial Registration: ClinicalTrials.gov, identifier: NCT05408793.

## 1. Introduction

Autistic spectrum disorder (ASD) is a neurodevelopmental disorder characterized by impairment in reciprocal social interaction, language dysfunction, and restricted interests, associated with behaviour problems. The prevalence is 62 in 10,000 in the general population [1]. ASD is often linked with functional impairment, and increased risk of psychiatric and medical morbidity [2]. Furthermore, ASD causes significant distress and mental health-related problems in the caregivers of people with ASD [3]. These negative detrimental effects will inevitably increase the global disease burden on our health care system, and thus, there is a pressing need to formulate evidenced-based, robust interventional studies to restore optimal wellbeing for this at-risk, vulnerable population.

Meanwhile, the exact underlying pathophysiology of ASD remains unknown. There was no effective and specific pharmacological treatment for core symptoms of ASD [4]. Conventional treatment for ASD consists of behavioural intervention and social skill training; these treatment options are time-consuming and labour-intensive. Therefore, a new, innovative but effective treatment alternative that is well-tolerated by ASD adolescents is warranted.

Transcranial pulse stimulation (TPS) is the latest NIBS used to stimulate the brain by inducing ultrashort ultrasound waves to the treatment region of the brain. TPS has been proven effective in the treatment of Alzheimer’s disease in a recent multicentre European study [5]. Study findings reported significant improvements in memory and cognition, a reduction in depressive symptoms [6], and a reduction in cortical atrophy [7]. Another local pilot open-label RCT also proved that TPS is effective in significantly reducing depression severity in adults diagnosed with major depressive disorder [8] in Hong Kong. Nonetheless, there is so far no further study using TPS evaluating the efficacy and safety on young adolescents with ASD. This research gap has given us the impetus to execute this trial.

### 1.1. Objectives

The aims of this study will be (1) to evaluate the efficacy and tolerability of TPS on adolescents (age 12–17) with ASD in Hong Kong; (2) to examine the association between TPS and ASD core symptom severity, executive functions, and social functions; and (3) to examine the brain functional connectivity changes immediately after the 2-week TPS treatment via neuroimaging.

### 1.2. Hypotheses

#### 1.2.1. Primary Hypothesis

Participants in the verum TPS group will have a significant reduction in Childhood Autism Rating Scale (CARS) score at posttreatment compared with the sham TPS group and be maintained at the 1-month and 3-month follow-ups.

#### 1.2.2. Secondary Hypotheses

Participants in the verum TPS group will have significant improvement in the Autism Spectrum Quotient (AQ) compared with the sham TPS group, which will be maintained at the 1-month and 3-month follow-ups.Participants in the verum TPS group will have significant improvements in the Social Responsiveness Scale (SRS) compared with the sham TPS group, which will be maintained at the 1-month and 3-month follow-ups.Participants in the verum TPS group will have significant improvement in the Faux Pas Recognition Test compared with the sham TPS group, which will be maintained at the 1-month and 3-month follow-ups.Participants in the verum TPS group will have significant improvement in the Stroop test compared with the sham TPS group, which will be maintained at the 1-month and 3-month follow-ups.Participants in the verum TPS group will have significant improvement in the Clinical global impression—severity and improvement scale (CGI-S and CGI-I) compared with the sham TPS group, which will be maintained at the 1-month and 3-month follow-ups.Participants in the verum TPS group will have significant brain function connectivity changes at posttreatment fMRI and resting-state MRI compared to the sham TPS group, which will be maintained at the 1-month and 3-month follow-ups.

## 2. Materials and Methods

### 2.1. Trial Design

This proposed study is a two-armed, randomized, double-blind, sham-controlled trial evaluating the efficacy and tolerability of a 2-week TPS treatment on ASD among adolescents. This study’s trial design strictly complies with the Consolidated Standards of Reporting Trials (CONSORT) statement [9] and Good Clinical Practice. Participants will be randomly allocated into the verum TPS group or sham TPS group. All the participants’ parents will be informed about the randomization procedures and that they have a 50% chance of receiving the verum TPS or the sham TPS. This study will be conducted in accordance with the Declaration of Helsinki [10]. Both groups will be measured at baseline (T1), immediately after the 2-week intervention (T2), and at 1-month (T3) and 3-month (T4) follow-ups [11] (Figure 1). We registered this trial with ClinicalTrials.gov on 7 June 2022 (NCT05408793).

### 2.2. Subjects

Participants will be recruited using a QR code flyer embedded with an online application form. This QR code flyer will also be flagged up in communal areas on campus in the research sites and collaborative universities including the Hong Kong Polytechnic University (HKPU), University of Hong Kong (HKU), and The Educational University of Hong Kong (EdUHK). The recruitment period will span three months. Participants will require parental written consent for TPS treatment and neuroimaging. Both participants and their parents will be informed that the TPS treatment study will involve an off-label treatment, and the possible risks and side effects will be clearly explained in the Information Sheet.

### 2.3. Inclusion Criteria

To be eligible, participants should (1) be 12–17 years of age, (2) be of Chinese ethnicity, (3) have an ASD diagnosis according to the 5th Edition of the Diagnostic and Statistical Manual of Mental Disorders (DSM-5), (4) not have any change in their drug regime, and (5) currently take prescribed psychotropic medications for ≥3 months.

### 2.4. Exclusion Criteria

Participants who (1) have a DSM-5 diagnosis other than ASD; (2) have concomitant major medical conditions; (3) have neurological problems (e.g., brain tumour or brain aneurysm); (4) have haemophilia or other clotting disorders, or thrombosis; (5) have a metal implant in the brain/brain treated region; (6) undertake corticosteroid treatment in the past 6 weeks prior to the first TPS treatment; or (7) have a Childhood Autism Rating Scale (CARS) score of 30 or below (i.e., no ASD) will be excluded from this study.

### 2.5. Sample Size

Based on a similar RCT design (4), the estimated effect size of repeated transcranial magnetic stimulation is 0.5. Nonetheless, this study is the first study evaluating TPS on ASD. Hence, we hypothesize a small effect size (0.3) on this pilot study. We used G*Power 3.1.9.4 to estimate the sample size for this study. Considering a similar study using rTMS with an effect size of 0.5, we decided to use 0.5 effect size in this first study. Thus, the sample size required is 34 in this study (17 subjects in each group).

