### 2.7. Randomization, Allocation, and Masking

Block randomisation will be used in this study. Each block will consist of 6 participants at a 1:1 ratio between the two groups (total: 6 blocks). In the randomisation procedure, each participant will be assigned a serial reference number generated by a computer. These numbers will not be decoded until the intervention group is assigned. An offsite statistician who is an independent team member, who will not be involved in the enrolment, intervention, or assessments, will perform the randomization process. Participants and research assistants who will be responsible for assessment and data analysis will be blinded to the group allocation (Figure 1). Participants will be asked to guess their treatment allocation in the 6th TPS session to determine the success of the blinding [12].

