## 3. Statistical Analyses

Chi-squared tests and *t*-tests will be performed for the categorical and continuous variables, respectively, to examine the presence of any group differences in the demographics and clinical profiles between the treatment and sham groups at baseline. A two-way analysis of variance (ANOVA) with repeated measures will be used to examine the effect of time and treatment conditions on the CARS scores and other secondary outcomes across various assessment time points. Post hoc analyses will also be performed using Bonferroni corrected *t*-tests to investigate the improvements in all outcome variables in pairwise comparisons across various assessment time points. The level of statistical significance will be set at a *p* value < 0.05. Intention-to-treat last-observation-carried-forward scores will be used for the analyses. Missing data will be managed by multiple imputation. All computations will be performed using SPSS for Windows, version 25.0.

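### Section 2.5 gives two unreconciled planning effects and calls 34 the required size at 0.5 without naming the metric; read as a between-arm difference of 0.5 SD, 34 is not supported

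*Protocol article*

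**What the plan says.** Section 2.5 takes an effect size of 0.5 from a trial of repeated transcranial magnetic stimulation. Because TPS is untested in ASD, it then lowers its expectation: "Hence, we hypothesize a small effect size (0.3) on this pilot study". After naming the software ("We used G*Power 3.1.9.4 to estimate the sample size for this study"), it goes back to the magnetic stimulation figure: "we decided to use 0.5 effect size in this first study". The conclusion is: "Thus, the sample size required is 34 in this study (17 subjects in each group".

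The section does not name the effect-size metric, the test, the target power or a within-person correlation.

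The comparison to be powered is between arms. Section 1.2.1 predicts a "significant reduction in Childhood Autism Rating Scale (CARS) score at posttreatment compared with the sham TPS group", maintained at 1 and 3 months. Section 2.7 allocates 1:1. Section 3 plans a two-way repeated-measures ANOVA over the assessment times and fixes the level: "The level of statistical significance will be set at a *p* value < 0.05".

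**The concern.** There are two problems in one paragraph. First, 0.3 is adopted because the treatment is new in this condition. It is then dropped for the figure it was meant to discount, with no reason that reconciles the two. Second, 34 is presented as what 0.5 requires. A reader will take 0.5 as half a standard deviation between verum and sham, and on that reading 34 is far below what a simple two-arm comparison needs.

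What is at stake is interpretation. If readers believe the trial was large enough to find 0.5 SD, they may take a non-significant CARS result as evidence against an effect of that size.

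**Working it through.** **Inputs.** From Section 2.5: effects 0.5 and 0.3, and N = 34 (17 per arm). From Section 2.7: 1:1 allocation. From Section 3: level 0.05. Assumed because not stated: two-sided testing, 80% power, and the correlations shown below.

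**Step 1. Where 34 comes from.** Three G*Power-type calculations give exactly 34 at 80% power and two-sided 5%. All have the same noncentrality, 8.5.
- Paired or one-sample t-test, dz = 0.5: 34 × 0.5² = 8.5. Power is 80.8% at N = 34 and 79.5% at N = 33. This test has no sham arm.
- Two-group F test, Cohen's f = 0.5: 34 × 0.5² = 8.5, power 80.7%. For two equal groups d = 2f, so this is a difference of 1.0 SD.
- Two-group by two-time interaction, f = 0.25, correlation 0.5: 0.25² × 34 × 2 / (1 − 0.5) = 8.5, power 80.7%. At correlation 0.5 the SD of change equals the SD of a single score. A two-sample test on change has noncentrality (17/2)δ², and setting this to 8.5 gives δ = 1.0 SD between arms in change.

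**Step 2. 0.5 as a between-arm difference, one visit, unadjusted.**
- Normal approximation: n per arm = 2(1.960 + 0.842)² / 0.5² = 62.8, so 63. The exact noncentral t gives 64 per arm (128 in total). At 0.3 the exact figure is 176 per arm.
- Power with 17 per arm: noncentrality 0.5 × √(17/2) = 1.458 on 32 df gives 29.3% (41.4% if one-sided). At 0.3 it is 13.6%; at 1.0 it is 80.7%.
- Difference detectable with 80% power: 0.99 SD (0.87 SD if one-sided).
- Unadjusted 95% CI half-width: 2.037 × √(2/17) = 0.70 SD.

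**Step 3. Analyses that use baseline or all visits, 0.5 SD, 17 per arm.** Equal correlation r between visits is assumed. The last two rows also assume a constant 0.5 SD effect at T2, T3 and T4, and the interaction row assumes sphericity. The adjusted rows keep 32 df, ignoring the one lost to the covariate.
- Baseline-adjusted, one visit: effective d = 0.5 / √(1 − r²), that is 0.577, 0.700 and 0.833.
- Four-visit group-by-time interaction, between-arm differences (0, d, d, d): noncentrality 8.5 × d² × 0.75 / (1 − r) on 3 and 96 df.
- Mean of the three follow-up visits, baseline-adjusted: effective d = 0.5 / √((1 + 2r)/3 − r²), that is 0.775, 0.898 and 1.050.

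| Analysis | r = 0.5 | r = 0.7 | r = 0.8 |
|---|---|---|---|
| One visit, baseline-adjusted | 37% | 51% | 65% |
| Four-visit interaction (test family of Section 3) | 28% | 45% | 63% |
| Three-visit mean, baseline-adjusted | 59% | 72% | 84% |

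Over a wider range, r = 0.3 to 0.9, the interaction runs from 21% to 92%. With baseline adjustment at one visit and r = 0.7, the detectable difference is 0.99 × √(1 − 0.49) = 0.71 SD. For that analysis to reach 80% power at 0.5 SD, r must be about 0.86.

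**The case against.** The strongest defence is that the metric is not stated, so 34 may be a correct G*Power output. Two of the three routes to 34 are two-arm designs. One of them, the interaction with f = 0.25, belongs to the family of tests that Section 3 plans, and 0.25 is the usual two-group conversion of d = 0.5. That stands: the origin of 34 cannot be settled from the text, and an arithmetic slip is not shown. It does not rescue the claim at 0.5 SD, because both two-arm routes imply about 1.0 SD between arms. The only textual pointer to the metric is that 0.3 is called small. That fits a standardized mean difference; on the f scale 0.3 lies above the conventional medium value of 0.25. It is a pointer, not proof.

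A second defence is that 29% is not the power of the planned analysis. This also stands. The figure is for one visit without adjustment, and the table shows higher power for most other choices, above 80% in one of them. No correlation is stated that would let the authors rely on this.

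A third is that this is a pilot reported in a condensed article, and details of the calculation may sit elsewhere. A pilot need not have 80% power, and missing detail alone would be no finding. But the article itself prints a required size and two conflicting effects.

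A reader might go further and infer that the plan is wrong by a factor of two in effect size (0.99/0.5) or nearly four in sample size (128/34), or that the trial has 29% power. The documents do not support either statement without conditions. The first holds only if 0.5 is a standardized between-arm difference and the comparison is unadjusted at one visit. The second depends on the analysis and the correlation.

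**Conclusion.** The concern holds in a limited form. Section 2.5 does not reconcile 0.3 with 0.5, and it does not support 34 as the size required for a between-arm difference of 0.5 SD. Every 80%-power route found to exactly 34 is either a one-group paired test or a two-arm calculation implying about 1.0 SD.

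On the standardized-difference reading, the unadjusted single-visit shortfall is 17 against 64 per arm. Under the more efficient analyses it narrows by an amount that turns on a correlation the document does not give. The conclusion assumes 80% power and two-sided 5%; one-sided testing raises the unadjusted power at 0.5 SD only to 41%. With an unadjusted half-width of 0.70 SD, an estimate near zero would have an interval that still contains 0.5 SD.

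**What to change.** Keep 34 and rewrite Section 2.5:
- Choose between 0.3 and 0.5 as the planning effect, or explain the role of each.
- Identify the metric of 0.5 and the calculation that produced 34.
- Replace the statement that 34 is required with the between-arm CARS difference that 17 per arm can detect in the planned analysis. For orientation, this is about 1.0 SD unadjusted at one visit and about 0.7 SD with baseline adjustment at an assumed correlation of 0.7.
- Give the power at 0.5 SD as a range over the assumed correlation.
- Add that a non-significant result does not exclude an effect of 0.5 SD, and quote the expected half-width of about 0.70 SD unadjusted.

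The cost is one rewritten paragraph and a less favourable stated figure. No participants are added and no analysis changes.

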### 2.6. Screening and Self-Administered Questionnaire

Participants’ parents will complete a QR code online application form soliciting sociodemographic information (age, gender, educational background, monthly family household income, living circumstances, school year, participant’s psychiatric history and duration of ASD diagnosis (in years/months), age of diagnosis, duration of taking prescribed medications (in years/months), current drugs and dosages, and family history of psychiatric disorder).

Eligible subjects will then fill in the online screening tool (Childhood Autism Rating Scale) (CARS); those with a CARS total score > 30 will be recruited. Subjects’ medical history, treatment regime, and developmental history will be obtained by direct enquiry with subjects’ parents by zoom interview prior to neuroimaging and TPS treatment. Both participants and parents will be interviewed by the principal investigator (PI) and the research personnel. Parents need to hold a valid medical certificate of his/her children’s ASD diagnosis (year/month) and show the most recent prescribed formulation sheet to the research team during the online interview. Any parent who fails to show these documentary proofs will not be invited to participate in this trial.

### 2.7. Randomization, Allocation, and Masking

Block randomisation will be used in this study. Each block will consist of 6 participants at a 1:1 ratio between the two groups (total: 6 blocks). In the randomisation procedure, each participant will be assigned a serial reference number generated by a computer. These numbers will not be decoded until the intervention group is assigned. An offsite statistician who is an independent team member, who will not be involved in the enrolment, intervention, or assessments, will perform the randomization process. Participants and research assistants who will be responsible for assessment and data analysis will be blinded to the group allocation (Figure 1). Participants will be asked to guess their treatment allocation in the 6th TPS session to determine the success of the blinding [12].

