### 2.8. Interventions

The TPS intervention venue will be located at the Integrative Health Clinic (IHC), the Hong Kong Polytechnic University. A licensed mental health practitioner (PI: [name]) will deliver the TPS intervention.

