#### 2.8.3. Sham–Control TPS

The procedure for sham stimulation will be identical, except that the castor oil used in the TPS group will be replaced by air-filled stand-off cushion in the hand piece. This sham device will be able to produce similar sound and stimuli on the subject’s head. Participants will be asked to continue their routine medication regimen throughout TPS intervention period.

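### A single published block size of 6 could let the PI, who helps screen, is the interventionist and is not listed as blinded, deduce the end of a block if enrolment is rolling

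*Protocol article*

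**What the plan says.** **Randomisation.** Section 2.7 gives the block structure: "Each block will consist of 6 participants at a 1:1 ratio between the two groups (total: 6 blocks"). An independent off-site statistician does the randomisation, and the reference numbers stay undecoded until the group is assigned. The same section names as blinded the participants and the research assistants who handle assessment and data analysis. The PI is not on that list.

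**Target.** Section 2.5 concludes that "the sample size required is 34 in this study (17 subjects in each group").

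**The PI at screening.** Section 2.6: "Both participants and parents will be interviewed by the principal investigator (PI) and the research personnel". This happens before neuroimaging and treatment.

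**The PI at treatment.** Section 2.8 says that the PI "will deliver the TPS intervention", and Section 2.9 again identifies the PI as the interventionist. Section 2.8.2 refers both to the interventionist moving the hand-piece and to trained staff giving the treatment.

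**Sham.** Section 2.8.3 keeps the procedure the same except that the "castor oil used in the TPS group will be replaced by air-filled stand-off cushion in the hand piece". The stated aim is similar sound and sensation for the participant.

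**Timing.** Recruitment lasts three months (Section 2.2) and a course of treatment takes two weeks (Section 2.8.4).

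**The concern.** Keeping the list off site hides future allocations from anyone who has no other information. It does not hide them from someone who knows the past allocations and the block size, because every block must end 3:3. Once three participants in a block have gone to one arm, the rest of that block is known.

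The article gives one person the means to do this. The PI is involved in screening, is named as the person who treats, works with equipment that differs by arm, and is outside the stated blinding. The block size is in print. Some exclusion criteria in Section 2.4, such as the one on serious coexisting illness, call for judgement, so there is room for a view about the next allocation to influence who is enrolled, even unintentionally.

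What is at stake is the comparability of the arms at baseline. With about 17 per arm, a few steered enrolments could shift it, and the baseline tests planned in Section 3 would have little power to show this.

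**Working it through.** **Inputs.** Block size 6, 1:1, six blocks (Section 2.7); 34 participants, 17 per group (Section 2.5); three months of recruitment (Section 2.2). Assumptions not in the article: rolling randomisation and treatment, and, for the worst case, a PI who knows every earlier allocation when the next candidate is interviewed.

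**1. List length.** 6 × 6 = 36 places against 34 participants. Five blocks would cover only 30, so six is the fewest that reach 34.

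**2. Certain allocations in a full block.** There are C(6,3) = 20 equally likely sequences. The allocations known for certain are those in the final run of one arm.
- The last one is always known: 1.
- The last two match: 2 × C(4,1)/20 = 0.4.
- The last three match: 2 × 1/20 = 0.1.
- Expected number: 1 + 0.4 + 0.1 = 1.5 of 6 (25%).

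**3. Best guess in a full block.** The guesser picks the arm with more places left. The chance of being right, given how many of the block's allocations are known:

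| Known | 0 | 1 | 2 | 3 | 4 | 5 |
|---|---|---|---|---|---|---|
| P(right) | 0.5 | 0.6 | 0.6 | 0.7 | 0.7 | 1.0 |

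The sum is 4.1 of 6 (68%). The closed form agrees: 3 + (64/20 − 1)/2 = 4.1.

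**4. Over 34 participants.** Five full blocks plus the first four places of the sixth. In those four places the certain number is 2/20 = 0.1 (the first three all in one arm), and the expected correct guesses are 0.5 + 0.6 + 0.6 + 0.7 = 2.4.
- Certain: 5 × 1.5 + 0.1 = 7.6; 7.6/34 = 22%.
- Guessed correctly: 5 × 4.1 + 2.4 = 22.9; 22.9/34 = 67%.

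**5. If the latest allocations are not yet known.** Suppose the last L allocations are unknown at the interview. The table in step 3 is then read L places later.

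| L | Certain per block | Correct per block | Certain of 34 | Correct of 34 |
|---|---|---|---|---|
| 0 | 1.5 | 4.1 | 7.6 (22%) | 22.9 (67%) |
| 1 | 0.4 + 0.1 = 0.5 | 3.6 | 2.5 (7%) | 20.2 (59%) |
| 2 | 0.1 | 3.4 | 0.5 (1%) | 19.1 (56%) |
| 3 | 0 | 3.2 | 0 | 18.0 (53%) |

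Thirty-four in about 13 weeks is 2.6 per week, so a lag of one week between interview and first session (an assumption) corresponds to L of about 2 or 3.

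**6. Split if enrolment stops at 34.** Five full blocks give 15:15. The first four of the sixth block are 2:2 with probability C(4,2) × C(2,1)/20 = 12/20 = 0.60. Otherwise they are 3:1 or 1:3, so an 18:16 split in either direction has probability 0.40. Efficiency relative to 17:17 is 4 × 18 × 16/34² = 1152/1156 = 0.997, a loss of about 0.3%.

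**The case against.** The case against has several parts.

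- **A reader might infer that the PI is unblinded and sees a visible difference at every session.** The article does not say so. It calls the trial double-blind, does not say whether the hand-piece difference can be seen or who fits the cushion, and in Section 2.8.2 mentions trained staff. This stands: the PI's knowledge of allocation is a reasonable inference from Sections 2.7, 2.8, 2.8.3 and 2.9, and no more than that. Nothing in the article describes masking of the operator.
- **Much of the eligibility check is documentary or scored.** It uses an online form, a CARS threshold, a medical certificate and a prescription sheet. Research personnel join the interview, and no section gives the PI the enrolment decision. This narrows the opening but does not close it, since some exclusions need judgement.
- **The percentages assume rolling enrolment and full, immediate knowledge.** This stands. With a lag of two or three participants almost nothing is certain, and if all were randomised in a batch after screening, nothing could be foreseen at screening. Three months of recruitment, two-week courses and one clinic make rolling enrolment plausible, but it is not stated.
- **A list of 36 for a target of 34 is ordinary.** Also right. A reader might take 36 against 34 as a serious contradiction; its only effect is a possible 18:16 split, which costs almost nothing.

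**Conclusion.** The concern holds in conditional form. A fixed, published block size of 6, combined with a PI who helps screen, is named as the interventionist and is not listed as blinded, leaves allocation partly predictable despite the off-site list. The size runs from 7.6 of 34 allocations certain and 67% guessed correctly (worst case: rolling enrolment, all earlier allocations known at once) down to none certain and 53% guessed correctly when the last three allocations are unknown. Even in the worst case more than three-quarters of allocations are not certain, so the documents do not support saying that the PI can foresee the list.

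Nor do they support saying that any resulting bias could never be found: Section 3 plans baseline comparisons. With 34 participants, though, it would be hard to detect and hard to correct. The change is worth making before enrolment. The difference between 36 and 34 is a side point of consistency.

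**What to change.** 1. Have the off-site statistician generate permuted blocks of randomly varying size, with the sizes withheld from anyone who screens or treats, and release each allocation only after eligibility and the baseline (T1) measures are recorded. The article is silent on the timing of release, and the full protocol may already cover it.
2. State in Section 2.7 whether the PI is blinded and who decides eligibility, and reconcile Sections 2.8, 2.8.2 and 2.9 on who operates the hand-piece. Varying the block size mainly removes the certain allocations. Someone who knows all past allocations can still guess the arm that is behind, without knowing any block size. The best protection against that is to have eligibility settled by someone who does not know earlier allocations.
3. Make the list fit the target. Either use sizes that sum to 34 and give 17:17, for example five blocks of 6 and one of 4 (30 + 4) or three of 6 and four of 4 (18 + 16), in undisclosed order, or state 36 (18 per group) in both Sections 2.5 and 2.7.

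The cost is a new list and a few sentences, with a slightly greater chance of a small arm imbalance.
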